## Abstract

**Introduction:**

Emotional disorders (such as anxiety and depression) are associated with considerable distress and impairment in day-to-day function for affected children and young people and for their families. Effective evidence-based interventions are available but require appropriate identification of difficulties to enable timely access to services. Standardised diagnostic assessment (SDA) tools may aid in the detection of emotional disorders, but there is limited evidence on the utility of SDA tools in routine care and equipoise among professionals about their clinical value.

**Methods and analysis:**

A multicentre, two-arm, parallel group randomised controlled trial, with embedded qualitative and health economic components. Participants will be randomised in a 1:1 ratio to either the Development and Well-Being Assessment SDA tool as an adjunct to usual clinical care, or usual care only. A total of 1210 participants (children and young people referred to outpatient, specialist Child and Adolescent Mental Health Services with emotional difficulties and their parent/carers) will be recruited from at least 6 sites in England. The primary outcome is a clinician-made diagnosis about the presence of an emotional disorder within 12 months of randomisation. Secondary outcomes include referral acceptance, diagnosis and treatment of emotional disorders, symptoms of emotional difficulties and comorbid disorders and associated functional impairment.

**Ethics and dissemination:**

The study received favourable opinion from the South Birmingham Research Ethics Committee (Ref. 19/WM/0133). Results of this trial will be reported to the funder and published in full in the Health Technology Assessment (HTA) Journal series and also submitted for publication in a peer reviewed journal.

**Trial registration number:**

ISRCTN15748675; Pre-results.

Strengths and limitations of this studyLarge real-world multicentre randomised controlled trial of the Development and Well-Being Assessment (DAWBA) Standardised Diagnostic Assessment tool as an adjunct to usual care versus usual care only.Trial procedures are carried out remotely with all data collection and the DAWBA completed online or via telephone, facilitating post-trial implementation into future service delivery models and routine clinical care.The embedded health economic component permits evaluation of both clinical and cost-effectiveness.Embedded qualitative work will support optimal delivery and implementation to enhance acceptability, effectiveness and long-term uptake.Participants, researchers and clinicians cannot be blinded to treatment allocation.

## Introduction

Emotional disorders cause considerable distress for affected children and young people (CYP) and their families, with adverse effects on family and peer relationships, quality of life, social involvement and activities, academic attainment and occupational opportunities, ultimately affecting life chances.^1–4^ Emotional disorders are frequently comorbid with other disorders,^2 5^ and are associated with self-harm and completed suicide. Effective evidence-based interventions are available but require appropriate identification of presenting difficulties to enable timely access to services and earlier recovery.^3^

The prevalence of emotional disorders has increased considerably over the past two decades.^1^ In the UK, CYP with clinically significant emotional difficulties may be referred to outpatient specialist Child and Adolescent Mental Health Services (CAMHS). However, insufficient information is a common reason for referrals being declined.^6^ There is limited evidence to inform optimal approaches to determine which referrals should be accepted, contributing to a large variation in acceptance rates.^6^ Likewise there is a lack of evidence on how best to conduct assessments for suspected emotional difficulties to optimise outcomes. Acceptance criteria and assessment procedures differ across services and there is no single standardised approach.

The multidisciplinary nature of CAMHS means CYP are assessed by practitioners from different professional backgrounds, with variations in training, ethos and conceptualisations of presenting difficulties. The type and scope of assessments offered vary. Assessments are often conducted by practitioners without formal diagnostic training^7^ and recording of potential diagnostic information can be influenced by patient, clinician and service-related contextual considerations.^8^ The validity and value of mental health diagnoses have been questioned, reflecting concerns around restricting service access,^9^ stigma or labelling.^7 10 11^ This can mean that in routine practice, assessments are often undertaken without the aim of making or recording a diagnosis.

However, National Institute for Health and Care Excellence (NICE) guidelines for management and treatment are usually based on diagnostic classification of disorders, so the ability to offer evidence-based interventions requires that the CYP’s difficulties are appropriately identified. Although NICE Quality Standards^12^ state that CYP with suspected depression should have the diagnosis confirmed and recorded, this is highly variable in practice.^7 13^ The use of diagnostic assessments has been recommended so that important problems are detected and appropriate interventions are offered.^3 11^ The NICE guidelines for depression have recommended the use of standardised diagnostic assessment (SDA) tools as potential adjuncts in the detection of depression within CAMHS.^14^ It has further been recommended that SDA tools should be used as an adjunct to clinical assessments, potentially at the point of referral receipt, to enable the allocation of cases to the most appropriate professional.^10 15 16^

One such SDA tool is the Development and Well-Being Assessment (DAWBA), a structured package of questionnaires and interviews which can be completed online or by telephone and yields algorithm-based diagnostic information.^17^ The DAWBA has established reliability and validity^17^ and has been widely used for screening, diagnosis and outcome measurement in research in both clinical and community settings,^18 19^ including trials of SDAs^20 21^ and large scale epidemiological research.^1 22 23^ A previous randomised controlled trial (RCT) using the DAWBA highlighted that, for emotional disorders, disclosing DAWBA diagnosis information to clinicians can improve the level of agreement between the DAWBA and clinical diagnoses, suggesting that the DAWBA can aid clinical detection of emotional disorders.^21^ It also improved detection of comorbid disorders. A UK trial found higher levels of agreement between DAWBA and clinical diagnoses, following disclosure of DAWBA information, in relation to anxiety disorders.^20^ Practitioners acknowledged that the additional information could supplement the assessment and aid detection of difficulties.^10^

Hence, it might be expected that the introduction of an SDA tool following CAMHS referral receipt could enable resources to be better targeted and a timely conclusion to assessments with a diagnostic decision, increase the likelihood that an appropriate evidence-based treatment is offered, and lead to improved outcomes and better experience of care for CYP and their families. However, there is limited evidence on the utility of SDA tools for informing optimal approaches to assessment within routine clinical practice.

### Aims and objectives

The aim is to evaluate the clinical and cost-effectiveness of the DAWBA SDA tool, as an adjunct to usual clinical care for CYP presenting with emotional difficulties referred to CAMHS.

Specific objectives are to:

Conduct an RCT to determine the effectiveness of the DAWBA as an adjunct to usual clinical care on diagnosis and treatment of emotional disorders, symptoms of emotional difficulties and comorbid disorders and associated functional impairment.Undertake an internal pilot to assess recruitment and acceptability.Include a qualitative component within the pilot phase to address:The feasibility of recruitment.The acceptability and usability of the interventions and procedure.How the intervention is used and could be refined for the main trial.Conduct a process evaluation alongside the main trial which will:Optimise the design and delivery of the DAWBA to enhance acceptability, effectiveness and long-term uptake.Identify the barriers and facilitators to implementation of the DAWBA from the perspectives of CYP, parents and CAMHS practitioners, managers and commissioners.Estimate cost-effectiveness of the use of the DAWBA versus usual care.Make evidence-based recommendations for assessment procedures within CAMHS and produce practice guidelines for clinical decision making around the referral acceptance and assessment processes.

## Methods and analysis

### Design

A multicentre, two-arm, parallel group RCT, with embedded qualitative and health economic components.

An internal pilot period, completed in the first 9 months of recruitment, will determine feasibility of recruitment and follow-up, assessed by the independent trial steering committee (TSC) against predefined stop/go criteria. The study start date is 1 November 2018 and end date is 31 October 2022.

### Setting

Recruitment will take place in at least six National Health Service (NHS) Trusts in England, providing outpatient multidisciplinary specialist CAMHS. Sites are geographically dispersed covering urban and rural areas, thus are likely to be sociodemographically representative of CAMHS referrals in England, enabling nationally generalisable findings.

### Recruitment and eligibility

#### Participant identification

The population is CYP presenting with emotional difficulties referred to CAMHS. Participants are identified through the usual referral pathways for the participating sites, which includes NHS and local authority managed Single/Central Point of Access referral points as well as referrals directly received and processed by CAMHS teams.

The STADIA (STandardised DIagnostic Assessment for children and young people with emotional difficulties) trial researchers (NHS personnel, based within the CAMHS SPA/triage team to carry out research activities on behalf of the team and authorised to access referral information) at each site review the referrals received by CAMHS to identify CYP presenting with emotional difficulties, according to a standard proforma (online supplemental appendix 1). Referrals that mentioned any current emotional difficulties will be included, regardless of the number, frequency or severity of the emotional difficulties. Potentially eligible participants are invited to consider taking part in the trial and provided with written information. The initial invitation follows standardised wording to ensure clarity and consistency of approach.

10.1136/bmjopen-2021-053043.supp1Supplementary data

Identification of participants takes place after referral receipt, but prior to referral acceptance (figure 1).

**Figure 1 F1:**
[figure not shown]
Participant flow. *For sites where the waiting time for the CAMHS acceptance decision usually exceeds 10 working days from referral receipt, recruitment activities may start and/or continue beyond 10 working days from referral receipt, providing the intervention period can be completed prior to the CAMHS referral decision. CAMHS, Child and Adolescent Mental Health Services; DAWBA, Development and Well-Being Assessment. STADIA, STAndardised DIagnostic Assessment for children and adolescents with emotional difficulties.

### Consent

Prior to consent, eligibility will be confirmed (box 1) during telephone contact with the local STADIA researcher, who will also provide written and verbal information about the trial, answer questions and support the electronic consent/assent process. Participants who are eligible and provide verbal consent to participation during the call will be provided with a personal link to the online electronic informed consent/assent form (table 1, online supplemental appendices 2 and 3, respectively), enabling them to provide written informed consent/assent.

10.1136/bmjopen-2021-053043.supp2Supplementary data

10.1136/bmjopen-2021-053043.supp3Supplementary data

Box 1Eligibility criteriaInclusion criteria for the children and young people (CYP)Aged 5–17 years.Referred to outpatient multidisciplinary specialist Child and Adolescent Mental Health Services (CAMHS).Presenting with emotional difficulties.If aged <16, has an eligible individual with parental responsibility (see parent/carer eligibility criteria below) willing and able to participate in the trial.If aged 16–17, has capacity to provide valid written informed consent.If aged 16–17 and participating without a parent/carer, able to complete the assessment tool in English.If aged 16–17 and participating without a parent/carer, access to internet and email or telephone.Exclusion criteria for the CYPEmergency or urgent referral to outpatient multidisciplinary specialist CAMHS (ie, requires an expedited assessment) according to local risk assessment procedures.Severe learning disability.Previously randomised in the STADIA trial.Inclusion criteria for the parent/carerIndividual with parental responsibility for the CYP referred to CAMHS; this will be the CYP’s mother or father, legally appointed guardian or a person with a residence order concerning the CYP.Adequate knowledge of the CYP to be able to complete the assessment tool (ie, known for at least 6 months).Has capacity to provide valid written informed consent.Access to internet and email or telephone.Able to complete the assessment tool in English.Exclusion criteria for the parent/carerLocal authority representatives designated to care for the CYP.

**Table 1 T1:** Consent and participation

Age of CYP referred to CAMHS	CYP aged <11	CYP aged 11–15		CYP aged 16–17	
Initial contact with	Parent/carer			Depends on contact details provided with the CAMHS referral*	
Consent provided by	Parent/carer	Parent/carer	Parent/carer	CYP AND parent/carer (optional)	CYP
Assent provided by	None	CYP (optional)	None	None	None
Participant(s)	Parent/carer only	CYP and parent/carer dyad	Parent/carer only	CYP and parent/carer dyad	CYP only
Primary participant†	Parent/carer	Parent/carer	Parent/carer	CYP	CYP
Secondary participant	None	CYP	None	Parent/carer	None
DAWBA completed by	Parent/carer	Parent/carer AND CYP	Parent/carer	CYP AND parent/carer	CYP
Research questionnaires completed by	Parent/carer report on CYP Parent/carer self-report	Parent/carer report on CYP Parent/carer self-report CYP self-report	Parent/carer report on CYP Parent/carer self-report	CYP self-report Parent/carer report on CYP Parent/carer self-report	CYP self-report

For all CYP aged <16 the initial contact about the study will be with the parent/carer. The involvement of CYP aged 11–15 will be at the discretion of the parent/carer.

*For CYP aged 16–17 if the CYP’s contact details are provided on the CAMHS referral the first contact about the study will be with the CYP who can choose to nominate a parent/carer to participate in the trial alongside them or participate alone. If the parent/carer’s contact details only are available the first contact will be with the parent/carer and the parent/carer will be asked whether the CYP can also be contacted but may choose to refuse this. The parent/carer will not be able to participate in the STADIA trial without the involvement or consent of the CYP.

†The primary participant is the person who must provide consent as a minimum requirement in order for randomisation to take place. Assent (of CYP aged 11–15) and parental consent (for CYP aged 16 and 17) may also be sought but is not mandatory and therefore will not be required prior to randomisation.

CAMHS, Child and Adolescent Mental Health Services; CYP, children and young people; DAWBA, Development and Well-Being Assessment; STADIA, STAndardised DIagnostic Assessment for children and adolescents with emotional difficulties.

The participation and consent/assent requirements for the trial are shown in table 1.

Participants are free to withdraw at any time and for any reason. Participants may withdraw from the intervention, follow-up questionnaires and/or data collection from records in any combination (eg, participants who do not complete the intervention will continue to be followed up, participants withdrawing from follow-up questionnaire completion may continue to consent for data collection from records). Withdrawn participants will not be replaced. Data collected prior to withdrawal will be retained and used in the analysis.

Where CYP aged 16 or 17 have consented for their own involvement they can continue to participate in the trial in the event of their parent/carer’s withdrawal, however, the parent/carer involvement would not continue should the CYP withdraw consent.

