### Randomisation and concealment

Participants will be randomised in a 1:1 ratio to either intervention or control. Allocation will be assigned using a minimisation algorithm balancing on recruiting site, CYP age (5–10, 11–15, 16–17 years) and sex, incorporating a probabilistic element to allocation. The allocation algorithm was created by Nottingham Clinical Trials Unit (NCTU) in accordance with their standard operating procedure. Allocation is concealed using an automated web system operated by NCTU.

Randomisation is automatically generated within the online system following submission, and automated verification, of baseline data by the primary participant. Participants are presented with their allocation and further instructions on-screen with email confirmation. Instructions for DAWBA completion are included for those in the intervention arm. Email confirmation is sent to the coordinating centre and site research team.

It will not be possible to blind participants, site researchers, clinicians and some trial staff to treatment allocation, but treatment allocation data will be restricted to those trial staff who require access to facilitate trial conduct. In particular, it will not be fully possible to blind researchers conducting data collection from records. However, any possible diagnoses identified from the CAMHS records will be recorded verbatim on the data capture form and will be subject to adjudication by the trial adjudication committee (members of the trial management group (TMG)). The committee will be blinded to treatment allocation and participant ID.

The risk of contamination between arms is considered low. Access to the DAWBA, and provision of the DAWBA report, is only provided to participants in the intervention arm. SDA tools are not current practice in standard care and it is unlikely that control participants will be asked to complete these at the point of referral receipt. DAWBA completion occurring outside the trial for control arm participants will be collected during follow-up.

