### Interventions

#### Development and Well-Being Assessment

The trial intervention is the DAWBA.^24^ The DAWBA has a modular structure, with only those modules relevant to emotional and comorbid disorders included; separation anxiety, specific phobia, social phobia, panic and agoraphobia, generalised anxiety, post-traumatic stress disorder, obsessive–compulsive disorder, depression, oppositional defiant disorder and conduct disorder. Whereas, the strengths and difficulties questionnaire, bipolar disorder and body dysmorphic disorder are not included in the STADIA-specific DAWBA report as these modules do not generate diagnostic predictions. No free-text responses are collected.

The DAWBA will be self-reported by participants via the secure, standalone online platform created and maintained by the DAWBA developer.^24^ Access is by a unique ID number and password, assigned at the point of randomisation via a stock control system integrated into the randomisation system, ensuring accountability of DAWBA slot allocation.

The DAWBA may be completed by the parent/carer and/or CYP aged 11+, depending on the consent and participation arrangements (table 1) DAWBA completion will be monitored and the STADIA researcher will support and encourage completion. Participants will be able to complete the DAWBA in a telephone call with the STADIA researcher if required. Participants are asked to complete all modules of the DAWBA presented to them. Should the DAWBA be only partially completed by respondents the report will be based only on fully answered modules with missing responses identified as such.

A trial-specific DAWBA report will be prepared for each participant, based on a standard, study-specific template (online supplemental appendix 4). The algorithm-derived diagnostic predictions will be used to highlight the likelihood of a CYP meeting International Classification of Diseases (ICD-10) criteria for the disorders assessed; the report is based entirely on the algorithm-derived predictions and is not clinically rated. The report will be sent to participants (via post or email) and CAMHS clinicians (via upload to the clinical record), as an adjunct to usual clinical practice.

10.1136/bmjopen-2021-053043.supp4Supplementary data

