Anxiety symptoms in the CYP	Revised CYP’s Anxiety Depression Scale (RCADS)	RCADS^33^ is a 47-item questionnaire that measures the reported frequency of various symptoms of anxiety and low mood. Each item is rated on a 4-point scale (never=0, sometimes=1, often=2, always=3). An overall anxiety and low mood score is generated, with separate sub-scale scores for separation anxiety, social phobia, generalised anxiety, panic, obsessive–compulsive disorder and major depression. RCADS demonstrates good psychometric properties.^34^ Total anxiety and depression scores range from 0 to 141. We will record scores for each of the six sub-scales. For analysis metric, we will use the total anxiety score. RCADS collected at baseline, 6 and 12 months post-randomisation.
Comorbid oppositional defiant/conduct disorder symptoms in the CYP	Strengths and Difficulties Questionnaire (SDQ)	SDQ^35^: A 25-item emotional and behavioural screening questionnaire for CYP. Each item is rated on a 3-point scale (not true, somewhat true, certainly true). Values of 0, 1 or 2 are assigned to each response. SDQ comprises five subscales and an impact supplement. The impact supplement asks effect of difficulties on homelife, friendships, education and leisure activities. SDQ has demonstrated reasonable psychometric properties.^36–39^ Scores on the ‘conduct problems’ subscale will be used in the analysis of this outcome. Subscale scores range from 0 to 10. SDQ collected at baseline, 6 and 12 months post-randomisation.
Functional Impairment in the CYP	SDQ	Impact supplement scores will be used to determine functional impairment. Impact scores range from 0 to 10. Collected at baseline, 6 and 12 months postrandomisation.
Self-harm thoughts in the CYP	CYP self-report self-harm measure	CYP will be asked to report the frequency of thoughts of self-harm. Frequency of thoughts of self-harm are rated over the last 6 months in the following categories and scored accordingly: Not at all (0) Once or twice Three or more times Collected at baseline, 6 months and 12 months post-randomisation.
Self-harm behaviours in the CYP	CYP self-report self-harm measure	CYP will be asked to report frequency of instances of self-harm behaviour. Frequency of self-harm behaviour are rated over the last 6 months in the following categories and scored accordingly: Not at all (0) Once Two or more times Collected at baseline, 6 months and 12 months post-randomisation.

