#### Statistical analysis

The primary approach to between-group comparative analyses will be by modified intention to treat (ITT) (ie, including all participants who have been randomised and without imputation of missing outcome data).

The primary comparative analysis will employ a generalised linear mixed model to compare the proportions in each group with a clinician-made diagnosis decision within 12 months of randomisation, adjusted for minimisation variables. The comparison will be presented as both an absolute (risk difference) and relative (risk ratio) effect, along with 95% CIs.

Secondary outcomes will be analysed using appropriate mixed effect regression models dependent on data type and will adjust for factors used in the minimisation and baseline value of the outcome where measured. For outcomes measured at multiple time points, these will be analysed using a mixed model with a treatment by time interaction to obtain estimates of treatment effect at each follow-up time.

Appropriate interaction terms will be included in the primary regression analyses in order to conduct subgroup analyses according to sex and age of the CYP.

Statistical analysis will be conducted using Stata V.17.0 (or later).

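### Secondary participants may enrol and give baseline data after the allocation is shown, so parts of some questionnaire outcomes are not guaranteed to be randomised comparisons

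*Protocol article*

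**What the plan says.** Table 1 of the protocol article (Consent) names a primary participant for each case: the parent/carer when the child is under 16, and the young person when aged 16–17. The footnote reads: "The primary participant is the person who must provide consent as a minimum requirement in order for randomisation to take place". The other member of a dyad is the secondary participant: the child aged 11–15, or the parent/carer of a 16–17-year-old. Their assent or consent "may also be sought but is not mandatory and therefore will not be required prior to randomisation". For the younger group: "The involvement of CYP aged 11–15 will be at the discretion of the parent/carer".

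On the order of events, Randomisation and concealment states: "Randomisation is automatically generated within the online system following submission, and automated verification, of baseline data by the primary participant". The next step is: "Participants are presented with their allocation and further instructions on-screen with email confirmation". The same section says that participants, site researchers and clinicians cannot be blinded.

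On outcomes, Table 2 takes self-harm from the young person: "CYP will be asked to report the frequency of thoughts of self-harm". Self-harm, the symptom scales, the parent/carer scales and quality of life are all scheduled at baseline, 6 and 12 months. Under Statistical analysis, the secondary models "will adjust for factors used in the minimisation and baseline value of the outcome where measured". Under Health economic analysis, the main cost-utility outcome combines the QALYs of the young person and the parent/carer.

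**The concern.** A comparison of randomised groups is protected when the set of people who report, and the covariates used, are fixed before anyone knows the allocation. Here the rule for secondary participants does not secure that. A parent/carer who has just seen the allocation may then decide whether the 11–15-year-old takes part. A parent/carer of a 16–17-year-old may join after the young person has seen it. If joining is related to both arm and severity, the reporters in the two arms differ from the start. If the secondary participant's first questionnaire is completed after allocation, the score entered as baseline may itself reflect knowledge of the arm, or the experience of completing the DAWBA.

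At stake are parts of several questionnaire secondaries, and the share of the joint QALY outcome that rests on secondary participants.

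**Working it through.** **Step 1: who is exposed.** This sets Table 1 (Consent) beside Table 2 (Secondary outcomes).

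| Report | Reporter's role | Baseline guaranteed before allocation? |
|---|---|---|
| Primary outcome, referral, diagnosis and treatment outcomes from records | not applicable | unaffected |
| Parent/carer reports, child under 16 | primary | yes |
| Self-report, aged 16–17 (including self-harm) | primary | yes |
| Self-report, aged 11–15 (including self-harm) | secondary | no |
| PHQ-9, GAD-7, EQ-5D-5L of parents/carers of 16–17s | secondary | no |

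Self-harm is therefore exposed in its 11–15 part only. PHQ-9, GAD-7 and EQ-5D-5L are exposed only for parents/carers of 16–17s. For MFQ, RCADS and SDQ the article does not say which informant is analysed, so exposure there is uncertain.

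**Step 2: is there a plan figure to reproduce?** Not on this point: the article gives no uptake rates for secondary participants. The sample size (544 per arm, 1210 in total) concerns the record-based primary outcome and is not in question.

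**Step 3: a simple bound. All inputs are assumed.** Let proportions pC and pI of potential secondary participants join, with no true effect. Suppose every extra joiner in the intervention arm enters because of the allocation and scores d SD higher than the other reporters. Then

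bias = (pI − pC)/pI × d.

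With an assumed 250 reporters per arm, SE = √(2/250) = 0.089 SD. The false-positive rate at two-sided 5% is 1 − Φ(1.96 − bias/SE) + Φ(−1.96 − bias/SE).

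| pC, pI, d | Bias (SD) | False-positive rate |
|---|---|---|
| 50%, 55%, 0.3 | 0.05/0.55 × 0.3 = 0.027 | 6% |
| 50%, 60%, 0.5 | 0.10/0.60 × 0.5 = 0.083 | 15% |
| 40%, 55%, 0.5 | 0.15/0.55 × 0.5 = 0.136 | 33% |

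**Step 4: a simulation, also on assumed inputs.** Severity is standard normal and the true effect is zero. Joining follows a logistic model, with 60% joining in control and 70% in intervention at average severity. There are 2 million simulated people per arm. Entries are intervention minus control, in SD.

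| Log-odds of joining per SD of severity | All decide after allocation | Half decide before | All decide before |
|---|---|---|---|
| 0.3, intervention only | 0.089 | 0.050 | 0 |
| 0.5, intervention only | 0.146 | 0.080 | 0 |
| 0.3, both arms | −0.030 | −0.015 | 0 |

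With 60% joining in both arms and no relation to severity, the bias is 0 throughout. With an assumed 200 reporters per arm, SE = √(2/200) = 0.10. A bias of 0.05, 0.10 or 0.15 SD then gives false-positive rates of about 8%, 17% and 32%.

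**Step 5: what the figures leave out.** They are unadjusted. They describe only the exposed part; in an outcome pooled over ages, the bias shrinks in proportion to the share of exposed reporters. The sign follows from the assumed joining pattern and could go either way.

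**The case against.** The strongest reply is that a permission is being read as a practice. The footnote may mean only that an optional signature does not hold up randomisation. The Consent section describes a telephone call before consent in which the researcher explains the trial and supports the electronic consent and assent process. A 16–17-year-old contacted first can choose then whether to nominate a parent/carer. Many dyads may be settled before allocation. The participant-flow figure, the data-collection schedule and the full protocol are not shown and may set a time window. This stands: the article does not say that late joining occurs, still less how often.

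A reader might infer that researchers in the intervention arm actively bring in secondary participants. The section on the DAWBA does not support that. It says: "DAWBA completion will be monitored and the STADIA researcher will support and encourage completion". This concerns completing the tool by those already taking part, not obtaining new assent. A difference in motive between the arms is plausible, because only intervention dyads have a DAWBA to complete, but it is an inference.

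Adjustment may also help. A score taken soon after allocation could absorb much of a severity imbalance, and the self-harm items look back six months, so an early answer mostly covers time before randomisation. This stands in part: the article sets no limit on how late such a score may be.

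Finally, the choice of informant for the symptom scales is ordinary SAP content and is not a fault of the article. Making self-report by 11–15s merely supportive would be a trade-off, not a correction. What remains after these replies is a stated enrolment order. A SAP can flag late joiners, but it cannot recover a join decision or a baseline that was not collected before allocation.

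**Conclusion.** The point holds in limited form. The stated rules allow secondary participants to enter and give baseline data after the primary participant has seen the allocation, with no cut-off in the article. The two exposed parts identified in the table are therefore not guaranteed to be randomised comparisons, and their baseline covariate may be a post-randomisation value.

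A reader might go further and conclude that the self-harm and self-report outcomes as a whole come from a set selected after randomisation. The documents do not support this, because 16–17-year-olds, and parents/carers of under-16s, must submit baseline data before allocation.

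The size of any bias cannot be derived from the documents. It is zero if joining precedes allocation or is unrelated to arm. It is about 0.03 to 0.15 SD if everyone joins afterwards under the assumed joining patterns, and smaller if only some do. Severity is moderate: some questionnaire secondaries and part of the joint QALY outcome are affected. The sample size and main conclusion are not, so this is not a must-fix.

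**What to change.** (a) For any remaining recruits, add an item to the primary participant's online baseline form that records, before the allocation is released, whether a secondary participant will be invited. Randomisation need not wait for that person's signature. This matters because the caption to Figure 1 requires the intervention period to finish before the referral decision.

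(b) Time-stamp each secondary participant's consent or assent and baseline questionnaire relative to randomisation, and report uptake by arm. For those already recruited, this assumes that the online system holds the time stamps.

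(c) State that a value recorded after allocation is not treated as a pre-randomisation baseline. For the exposed outcomes, add a sensitivity analysis limited to reporters whose consent or assent and baseline both precede randomisation.

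The cost is one extra form item, some extra analysis and reporting, and lower precision in the sensitivity set because late joiners drop out of it. If uptake proves similar between arms and nearly all secondary baselines precede allocation, the table from (b) will largely settle the matter.
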